#### Secondary objectives

To assess the effect of standard type 1 treatment (insulin) on average number of times the fasting plasma glucose level is above 8 mmol/l (141 mg/dl), quality of life [ADDQol [12]], proportion of patients with insulin dependence (as judged by C peptide level below 0.38 ng/ml [13]), GAD antibody level, HOMA, hypoglycaemic events (particularly hypoglycaemic events), weight/blood pressure/total cholesterol and inflammatory markers in LADA patients compared to standard type 2 diabetes treatment.

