#### Intervention

Insulin arm: Patients will be given advice on diet and exercise and life style and will be started on NovoMix 30, one dose of 6 U at the evening/main meal. Dose will be adjusted in increments of 2–6 U depending on fasting glucose level [See Figure 1]. When total dose equals 16 U patient will be started on 4 units with breakfast and continue with 16 units with evening meal. Breakfast and/or evening meal dose will be adjusted where necessary at increments of 2–6 U depending on fasting and/or pre-evening meal glucose level. [See Figure 1 below]. Patient needs to keep a daily diary of insulin doses taken.

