**Figure 1 F1:**
[figure not shown]
Insulin treatment.

All patients will see a dietician before insulin treatment is initiated. Patients will be contacted weekly by phone in the first month, fortnightly in the second month and once a month thereafter. Patients will monitor their blood glucose twice a day for 3 days of the week.

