Life style modification and Glitazone [Rosiglitazone]. Patients with a HbA1_c _of 7% or above will be given 4 mg once per day for 3 months. If after a 3 month period the HbA1_c _remains at 7% or above then titrate to maximal dose of 4 mg twice per day with or without Metformin. If HbA1_c_remains at 7% or above for an additional 3 months then move to step 4. Therefore, glitazone monotherapy will be used if Metformin intolerant otherwise glitazone will be added to the metformin (as per standard practice). Before initiation of Rosiglitazone a repeat medical history will be taken with special emphasis on cardiovascular disease, if patients have a history of cardiovascular disease (defined as IHD, PVD) they will not be initiated on Rosiglitazone but will move directly to Step 4 (insulin). Patients on rosiglitazone will be monitored using the adverse events form, for symptoms of heart disease specifically for chest pain and shortness of breath. Any adverse events suggestive of heart disease will result in Rosiglitazone being discontinued and the patient moving to step 4.

##### Step 4

Life style modification and insulin therapy (oral agents will be stopped). Titration will be based on fasting blood glucose level (as given in Figure 1). The initiation of insulin will the same as for the insulin arm and will follow the protocol detailed above.

All tablet treated patients will be asked to keep a diary of daily medication and record blood glucose levels weekly.

All changes in medication will be notified to the patients GP.

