### Follow up procedure

Patients are seen for a screening visit where they are asked to give consent and have baseline tests regarding inclusion/exclusion criteria. They return after 2 weeks for randomisation and are followed every 3 months there after. [See Figure 3]

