### Analysis plan

The statistical evaluation will be performed using SPSS. All data will be listed and trial summary tables will be provided. Summary statistics will be presented by group.

The primary analysis will be an intention to treat analysis examining (1) the average change in C peptide level at the end of the study in both groups and (2) the average change in HbA1c level at the end of the study in both groups. A linear regression model will be used to examine the effect of baseline GAD level, age, sex and baseline fasting C-peptide or HbA1c level as covariate and a treatment term on the change in HbA1c and C-peptide levels. In addition, repeated measures analysis (area under the curve, maximum minus minimum, time taken to maximum, time taken to minimum and slope) for C-peptide and HbA1c will be performed. ANOVA for repeated measurements with be used when variables are normally distributed. Otherwise, log transformations or non parametric tests will be employed.

Data will be collected by research nurses under the medical care of [name] and [name] and monitored by the trial co-ordinator. The analysis will be performed by [name] who will be blind to treatment group until after all analysis has been completed and interpreted. The CONSORT statement will be followed and used for reporting results.

Secondary analysis will include: Intention to treat analysis of :

(1) Average change in fasting C-peptide level in the insulin group compared to the control (best alternative care) group at 12 months.

(2) Average change in HbA1c level in the insulin group compared to the standard care group at 12 month. Data will be presented using confidence intervals only.

(4) Quality of life in the insulin vs standard care groups

(5) Number of events of fasting glucose being above 8 in the insulin vs standard care arm.

(6) Proportion of patients with a C-peptide below 0.38 ng/ml at baseline, 12 months and 24 months.

(7) Level of inflammatory markers in the insulin vs standard care arm

(8) GAD levels of insulin vs standard care

(9) Episodes of adverse events in the insulin vs standard care arms

(10) Weight gain in terms of BMI and waist/hip ratio in both groups

(11) HOMA or insulin resistance in both groups

We shall use two sided tests and confidence intervals for all comparisons.

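### The secondary outcome counting fasting glucose values above 8 mmol/l has no denominator and no stated source of readings, and its mg/dl equivalent is wrong (minor)

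*Protocol article*

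**What the plan says.** The outcome appears twice in the protocol article. The Secondary objectives describe it as the "average number of times the fasting plasma glucose level is above 8 mmol/l (141 mg/dl". The Analysis plan, secondary item (5), shortens this to "Number of events of fasting glucose being above 8 in the insulin vs standard care arm", without the specimen or the unit. Neither place says which readings are counted or what the count is divided by.

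Two possible sources of glucose readings are described:

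- **Home monitoring, which differs by treatment.** Under Intervention, in the text below Figure 1 (insulin treatment): "Patients will monitor their blood glucose twice a day for 3 days of the week". For the tablet arm, at the end of Step 4: "All tablet treated patients will be asked to keep a diary of daily medication and record blood glucose levels weekly". On Step 4 itself: "The initiation of insulin will the same as for the insulin arm and will follow the protocol detailed above".
- **Clinic visits, which are the same for all.** Under Follow up procedure: "They return after 2 weeks for randomisation and are followed every 3 months there after".

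**The concern.** A count of exceedances rises with the number of times a patient is measured as well as with glucose level. In this trial the prescribed frequency of home testing depends on treatment. An outcome defined as a bare count can therefore differ between arms with no difference in glycaemia, if home readings feed it.

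Even if they do not, a count without a denominator treats a patient with few samples as a patient with good control. At stake is a glycaemic secondary outcome that might appear to disagree with HbA1c only because some patients were observed more than others.

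The two units given for the threshold in the Secondary objectives also do not correspond, so one outcome definition carries two cut-offs.

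**Working it through.** **1. The threshold.** The plan's own figure is 141 mg/dl for 8 mmol/l. Glucose has a molar mass of about 180.16 g/mol, so mg/dl = mmol/l × 18.016.

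- 8 × 18.016 = 144.1 mg/dl (144.0 with the rounded factor 18).
- 141 / 18.016 = 7.83 mmol/l.
- The factor implied by the plan is 141 / 8 = 17.6, which no usual rounding gives.

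The stated figure is not reproduced. The gap is 3 mg/dl, about 2%.

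**2. Readings available if home diaries were counted.** Inputs:

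- Follow-up of 24 months (Primary objectives), about 104 weeks.
- Insulin: 2 tests a day × 3 days = 6 a week. The Intervention section adjusts insulin doses "depending on fasting and/or pre-evening meal glucose level". I therefore assume that one of the two daily tests is fasting, giving 3 fasting readings a week.
- Tablets: "record blood glucose levels weekly", read as one reading a week and assumed to be fasting. The text states neither.

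Fasting readings over the trial: insulin 3 × 104 = 312; tablets 1 × 104 = 104; ratio 312 / 104 = 3.0.

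Expected events = readings × P, where P is the share of fasting readings above 8, set equal in both arms. The plan gives no value for P, so a range is shown:

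| P (assumed) | Insulin, 312 readings | Tablets, 104 readings | Ratio |
|---|---|---|---|
| 0.1 | 31.2 | 10.4 | 3.0 |
| 0.2 | 62.4 | 20.8 | 3.0 |
| 0.3 | 93.6 | 31.2 | 3.0 |
| 0.5 | 156.0 | 52.0 | 3.0 |

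The ratio does not depend on P.

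**3. Dilution by Step 4.** Suppose a tablet patient who moves to insulin for w weeks takes up the insulin testing schedule. Step 4 says that initiation follows the insulin-arm procedure; that monitoring follows too is an assumption. That patient's fasting readings are then (104 − w) + 3w.

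- w = 26: 78 + 78 = 156; ratio 312 / 156 = 2.0.
- w = 52: 52 + 156 = 208; ratio 312 / 208 = 1.5.
- w = 78: 26 + 234 = 260; ratio 312 / 260 = 1.2.

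So 3.0 is an upper figure for fasting readings under these assumptions. The arm-level ratio depends on how many patients reach Step 4 and when, which cannot be known in advance.

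**4. Readings available if only visit samples were counted.** 24 months / 3 = about 8 follow-up visits in each arm, so the ratio is 8 / 8 = 1. The testing-frequency bias is gone.

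**5. Simulated check of steps 2 and 4.** With no true difference, 97 patients per arm (the Sample size figure) and P drawn for each patient from a Beta(1, 2) distribution (an assumption), a t-test on raw counts rejected at 5% in 100% of 2,000 runs with 312 against 104 readings. It rejected in 5% of runs with 8 against 8.

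**6. What remains with visit samples.** Withdrawn from study lists missing more than 3 visits without contact as a ground for withdrawal, so a patient who misses 3 and attends 8 − 3 = 5 stays in. At P = 0.2 that patient contributes 5 × 0.2 = 1.0 expected event, against 8 × 0.2 = 1.6 for a full attender. The ratio 5 / 8 = 0.625 holds for any P. Handling of missing and incomplete data carries the last value forward as the final value, or sets best and worst cases for HbA1c and C-peptide. Neither rule says what to do with an incomplete count.

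**The case against.** The strongest reply is that the outcome was never meant to come from diaries. The Secondary objectives say plasma glucose, whereas the self-monitoring instructions say only blood glucose and do not mention the outcome. Fasting glucose in the Intervention section serves dose adjustment. All patients attend every 3 months. HOMA and fasting C-peptide are both outcomes and imply fasting samples in both arms. Item (5) is a one-line shorthand for the objective, and its neighbours are just as brief. The schedule of visits (Figure 3) is not shown and may list fasting glucose. Count models and sample sources for a secondary outcome are often left to a fuller document.

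Most of this stands, and it rules out several stronger readings:

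- A reader might infer that the planned comparison is biased threefold against insulin. The document does not support that as fact, because nowhere does it say that diary readings are counted.
- A reader might go to sixfold by setting 6 weekly tests against 1. The outcome is fasting glucose, and about half of the insulin-arm tests would not be fasting, so that figure does not apply.
- A reader might add that unequal follow-up makes matters worse for insulin. Both arms have 24 months, and nothing indicates which arm, if either, would attend less.

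What the reply does not remove is that the article commits in two places to a count, under monitoring rules that differ by treatment, and does not exclude home readings. Nor does it remove the need for a denominator when visits are missed. The unit slip is not in dispute, but its effect is small, since item (5) uses 8 alone and no analysis uses 141.

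**Conclusion.** The point holds in a conditional form and is minor. The outcome is a raw count with neither a denominator nor a named source.

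- **If diaries were used,** the count would be biased against insulin by a factor of up to about 3. This rests on one fasting test per insulin test day and one fasting tablet reading a week, and it falls to 1.5 against a tablet patient who spends 52 weeks on Step 4 with insulin-arm testing.
- **If only visit samples were used,** which is the more natural reading of the Secondary objectives, that bias is absent. What remains is that missed visits and early withdrawal lower a patient's count for want of observation, to 5/8 of the full figure for a patient with 5 of 8 visits. This biases the arm comparison only if attendance differs between arms, which the document gives no reason to assume.
- **The conversion error is unconditional.** 8 mmol/l is 144 mg/dl, and 141 mg/dl is 7.83 mmol/l.

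None of this touches the primary outcomes.

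**What to change.** In Analysis plan item (5), state that the outcome is fasting plasma glucose above 8 mmol/l at the scheduled 3-monthly visits, and that self-monitoring readings are not counted. Analyse the number of exceedances over the number of valid samples for each patient, by binomial regression or by a count model with the log number of samples as offset. In the Secondary objectives, change the threshold to 8 mmol/l (144 mg/dl).

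This is a change of wording only, provided that fasting glucose is measured at those visits. The HOMA and fasting C-peptide outcomes imply that it is, but the visit schedule is not shown and should be checked. The downside is fewer readings per patient, about 8 instead of a diary series, so each patient's exceedance proportion is less precise. In return, the number of scheduled samples is equal in both arms, and the analysis allows for missed ones.

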**Methods/design:**

This is an open parallel group prospective randomised trial. Participants need to have a GAD antibody test results of 101 WHO units or more and a diagnosis of diabetes not requiring insulin at diagnosis. Participants will need to have been diagnosed within 12 months and not treated with insulin at study entry. They will be randomised to receive either insulin (NovoMix 30) or tablets (diet treated followed by metformin followed by glitazone (with or without metformin) followed by insulin). Primary outcome assessment will be for change in HbA1c and change in fasting C-peptide over 24 months. Secondary outcome measures will include Quality of life, GAD antibody levels, adverse events, inflammatory markers, insulin resistance, and markers of the metabolic syndrome.

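### The planned between-arm comparison of HOMA is confounded by current insulin injection, so on-insulin values cannot support a treatment effect on insulin resistance

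*Protocol article*

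**What the plan says.** The abstract names insulin resistance as a secondary outcome: "inflammatory markers, insulin resistance, and markers of the metabolic syndrome". The secondary objectives list "GAD antibody level, HOMA, hypoglycaemic events (particularly hypoglycaemic events") among the effects of insulin treatment to be assessed "in LADA patients compared to standard type 2 diabetes treatment". The analysis plan opens its secondary list with "Secondary analysis will include: Intention to treat analysis of", and item (11) reads "HOMA or insulin resistance in both groups". The same section applies two-sided tests and confidence intervals to every comparison.

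On exposure, the Intervention section says that insulin-arm patients "will be started on NovoMix 30, one dose of 6 U at the evening/main meal", with a breakfast dose added later. In the tablet arm, Step 4 is "Life style modification and insulin therapy (oral agents will be stopped"), started in the same way as in the insulin arm.

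The article does not say which HOMA index is meant, whether its input is insulin or C-peptide, or how values taken on injected insulin are to be treated.

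**The concern.** HOMA is an indirect measure. It infers resistance from fasting glucose together with the insulin that the patient's own pancreas is putting out. Injected insulin breaks that link in two ways. If fasting insulin is the input and the assay reads the injected product, the measured value includes insulin the patient did not secrete. If C-peptide is the input, or the assay does not read the product, the value reflects secretion that the injections may have suppressed.

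One arm injects from the start and the other only in part and later, so the distortion falls unequally on the arms. A difference in HOMA could then be reported as insulin worsening or improving resistance when resistance has not changed, and its direction could depend on a laboratory choice the article does not state.

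**Working it through.** **The plan's own figure.** The plan gives no number for HOMA. Its one sample size is for HbA1c: n per arm = 2 × (1.960 + 1.282)² × (1.5/0.7)² = 96.5, rounded up to 97, with power 90.1%. This reproduces the stated 97 and does not depend on HOMA.

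**Who is injecting, and when.**
- Insulin arm: from the start of treatment. Baseline values are free of injected insulin, because participants enter the study not on insulin.
- Tablet arm, failing every step at 3-month reviews: a patient starting Step 2 with HbA1c above 8% has two metformin periods and two rosiglitazone periods, 2×3 + 2×3 = 12 months. The slowest path is 3 (lifestyle) + 4×3 (metformin) + 2×3 (rosiglitazone) = 21 months. Both fall within the 24 months. A cardiovascular history or metformin intolerance can shorten the path. The share of the arm reaching Step 4 is not given.

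**Size, under stated assumptions.** Take HOMA resistance as proportional to fasting glucose × fasting insulin (or C-peptide), and hold true resistance constant. Let f be the injected share of measured insulin and s the proportional suppression of own secretion.
- Own insulin falls from I to I(1 − s).
- If the assay reads the injected product, measured insulin is I(1 − s)/(1 − f). At equal glucose, HOMA changes by the factor **(1 − s)/(1 − f)**.
- With C-peptide, or an assay blind to the product, the factor is **1 − s**.

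| f | s | Insulin input, product read | C-peptide, or product not read |
|---|---|---|---|
| 0.2 | 0.2 | 0.8/0.8 = 1.00 | 0.80 |
| 0.2 | 0.1 | 0.9/0.8 = 1.13 | 0.90 |
| 0.5 | 0.2 | 0.8/0.5 = 1.60 | 0.80 |
| 0.5 | 0.1 | 0.9/0.5 = 1.80 | 0.90 |

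**Sensitivity to glucose.** Insulin is titrated on fasting glucose, so equal glucose is itself an assumption. If glucose were 6.0 instead of 7.0 mmol/l (illustrative), every factor is multiplied by 6.0/7.0 = 0.86. The insulin-based range becomes 0.86 to 1.54, which includes values below 1.

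**From patient to arm.** These factors compare an injecting patient with a non-injecting one. With no tablet patient at Step 4, the full factor appears in the arm difference. If all were at Step 4 with the same factor, it would cancel. The true position lies between and shifts over follow-up.

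**The case against.** The strongest reply is that a journal article condenses the protocol. A few words on HOMA cannot be expected to fix the index, input, assay and visits, and the full protocol may use C-peptide or limit HOMA to values taken before insulin. That is fair on the missing details, and they are not the point here. What the article does state is an intention-to-treat comparison of the two arms with no limit for injected insulin. Changing the input alters the direction of the distortion but does not remove it. Limiting HOMA to values off insulin would leave the insulin arm with essentially only baseline values, so no randomised on-treatment comparison would remain.

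The second reply is that the magnitude is assumed. That stands. The document contains no insulin, C-peptide or HOMA values, and does not say whether the assay reads the injected product. A reader might hold own secretion fixed, use 1/(1 − f), and infer an inflation of 1.25 to 2.0. That ignores the suppression that the same argument relies on; with both included the range is 1.0 to 1.8 and contains no distortion at all.

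Third, HOMA is one item in a long secondary list, and no decision in the plan depends on it. That also stands and sets the weight of the point.

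**Conclusion.** The point holds as a minor correction to a secondary endpoint. As written, the arm difference in on-treatment HOMA is confounded by current insulin use to an unknown degree. Illustratively, an insulin-based HOMA changes by a factor of about 1.0 to 1.8 and a C-peptide-based one falls by 10% to 20%, with no change in true resistance. This rests on f of 20% to 50%, s of 10% to 20%, equal glucose and simple proportionality, none of which the document supplies.

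Three stronger readings are tempting but not supported:
- That HOMA would measure injected insulin instead of resistance. Some resistance signal would remain; it cannot be separated from the effect of injecting.
- That every insulin-arm value is affected. Baseline values precede insulin, and the section on withdrawal keeps in data collection some patients who stop treatment.
- That BMI, waist/hip ratio, blood pressure and cholesterol could serve as undistorted measures of resistance. They are not direct measures of it, and item (10) itself treats weight gain as an outcome that treatment may change.

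**What to change.** Amend item (11) and the matching secondary objective to:

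- name the HOMA index and its input (insulin, with the assay's reading of the injected product stated, or C-peptide);
- use HOMA at baseline as a description of the patients or as a covariate;
- report all post-baseline values descriptively, by arm and with current insulin use shown;
- state that no between-arm treatment effect on insulin resistance will be concluded from HOMA measured on insulin.

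Any summary in tablet patients not yet on insulin should be labelled a non-randomised subgroup. Step 4 is reached mainly through HbA1c staying at 7% or above, so those left behind are increasingly the better-controlled patients. BMI, waist/hip ratio, blood pressure and cholesterol should stay as outcomes in their own right and not be presented as substitutes for a resistance measure.

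The cost is a few lines of text and the loss of one nominal secondary between-arm result that could not have been interpreted. The primary analyses and the 97 per arm do not change.

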### Handling of missing and incomplete data

Data may or may not be missing at random. We shall compare patients with complete and missing data in sex, age and metabolic control (HbA1c) to test whether data are missing at random.

If data are missing at random and a participant does not attend follow-up visits, then the last recorded measure will be used as the final value. In cases were laboratory data is missing we will attempt to obtain values from the participants laboratory records supplied to their GP (using their NHS number in the diagnostics laboratory) unless they have actively withdrawn their consent for us to view their GP records.

If data are missing in a non-random way we shall compare the 'worst' case (high HbA1c and low c-peptide) and the 'best' case (normal HbA1c and normal c-peptide) to estimate confidence intervals for the final analysis.

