### Sample size

The study conducted in China [14] examined fasting C-peptide levels over 12 month, the average difference in C-peptide at 12 months was 0.18 nmol/l (stdev: 0.5 nmol/l) between the insulin vs the SU groups. To find a difference of 0.7% in average HbA1c (standard deviation = 1.5%) we would need 97 analysible people in the insulin and the standard care arms of the study (power 90%, significance = 5%). This would detect an average difference of 0.2 nmol/l in fasting C-peptide. As the power calculation is based on patients in China, we will re-calculate the sample size based on the standard deviation of the first 30 patients recruited in our study. We will examine the standard deviation of the HbA1c and the fasting C-peptide in all 30 patients at 3 months (regardless of treatment) in order to re-estimate the sample size assuming a difference of 0.7% in HbA1c and 0.2 nmol/l in fasting C-peptide.

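### The missing-data rule tests for missing at random with a comparison that cannot show it, then carries the last value forward if it passes and uses undefined best/worst cases if it fails

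*Protocol article*

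**What the plan says.** Protocol article, Handling of missing and incomplete data, lays down a three-part rule.

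- **Check.** Patients with complete and missing data are compared on sex, age and HbA1c "to test whether data are missing at random". No decision threshold is given, and neither C-peptide nor treatment arm is in the comparison.
- **If judged missing at random.** For a participant who stops attending, "then the last recorded measure will be used as the final value". Missing laboratory values are first sought from the laboratory records held for the GP.
- **If judged non-random.** "we shall compare the 'worst' case (high HbA1c and low c-peptide) and the 'best' case (normal HbA1c and normal c-peptide") to obtain confidence intervals for the final analysis. High, low and normal are given no numbers.

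The Analysis plan makes the intention-to-treat change at the end of the study primary for both C-peptide and HbA1c. It uses a linear regression on treatment, baseline GAD, age, sex and the baseline value of the outcome. Visits are every 3 months (Follow up procedure). The section on withdrawal asks for a termination visit with all final-visit assessments after premature discontinuation.

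**The concern.** The rule goes wrong at three points.

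1. **The check answers a different question.** A difference between completers and non-completers on observed variables contradicts MCAR. It is fully compatible with MAR, and no comparison of observed data can separate MAR from MNAR.
2. **LOCF does not follow from MAR.** It requires the outcome to stay flat after the last visit. The Background describes LADA as progressing slowly to insulin dependence, so a value from month 9 or 12 is not a month-24 value. This bites harder for C-peptide than for HbA1c, which is titrated in both arms.
3. **The branches are mismatched.** Missingness related to age, sex or HbA1c is what MAR methods handle, and age, sex and baseline value are already in the primary regression. Under this rule it triggers the bounds instead.

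At stake is the 24-month contrast on both primary outcomes in an open trial, where dropout may differ between insulin and tablets. LOCF can shrink a real effect or create one from dropout timing, and an observed-data pretest chooses which analysis is reported.

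**Working it through.** **Inputs from the article.** HbA1c: "To find a difference of 0.7% in average HbA1c (standard deviation = 1.5"%); "power 90%, significance = 5"%; two-sided ("We shall use two sided tests and confidence intervals for all comparisons"); "97 analysible people in the insulin and the standard care arms of the study", read as 97 per arm with equal allocation. C-peptide: target 0.2 nmol/l ("This would detect an average difference of 0.2 nmol/l in fasting C-peptide"), SD 0.5 nmol/l. **Assumed**, because the article gives no figures: dropout rate and timing, course of the outcome, best/worst values.

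**Step 1. The plan's own figure.** n = 2(1.96 + 1.2816)² × 1.5² / 0.7² = 96.5, so 97 per arm. It reproduces (power 90.1%). Standard errors: HbA1c 1.5√(2/97) = 0.2154; C-peptide 0.5√(2/97) = 0.0718.

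**Step 2. LOCF with a true effect.** Suppose the effect grows linearly to month 24 and a share d leaves both arms at mean month 12. LOCF then estimates effect × [(1 − d) + d × 12/24], and power = Φ(estimate/SE − 1.96).

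| Dropout | HbA1c estimate | Power | C-peptide estimate | Power |
|---|---|---|---|---|
| 0% | 0.70 | 90% | 0.20 | 80% |
| 5% | 0.68 | 89% | 0.195 | 78% |
| 10% | 0.665 | 87% | 0.19 | 75% |
| 20% | 0.63 | 83% | 0.18 | 71% |

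A simulation (97 per arm, 3-monthly visits, correlation 0.9 between adjacent visits, about 20% dropout) agreed: a true 0.70 became 0.61 under MCAR, 0.62 under MAR and 0.59 under MNAR.

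**Step 3. LOCF with no true effect.** Let C-peptide fall linearly by D in both arms, with dropout at mean month 12 of 10% in one arm and 20–30% in the other. Spurious difference = D × (1 − 12/24) × (difference in dropout). Type I error = P(|Z + bias/0.0718| > 1.96).

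| Fall D (nmol/l) | 10% vs 20%: bias, type I error | 10% vs 30%: bias, type I error |
|---|---|---|
| 0.2 | 0.010, 5.2% | 0.020, 5.9% |
| 0.3 | 0.015, 5.5% | 0.030, 7.0% |
| 0.4 | 0.020, 5.9% | 0.040, 8.6% |

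This is 5–20% of the 0.2 nmol/l target.

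**Step 4. The check.** The article does not say which HbA1c value or threshold is used; a t test on baseline HbA1c at 5% is assumed. In simulated trials with about 12% missing, dropout depended only on the last observed HbA1c, so the data were MAR by construction. The check declared them non-random as follows:

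| Log-odds of dropout per 1% HbA1c | Correlation between adjacent visits | Rejection |
|---|---|---|
| 0.8 | 0.9 | about 95% |
| 0.4 | 0.9 | about 50% |
| 0.8 | 0.6 | about 35–40% |
| 0.4 | 0.8 | about 30% |
| 0.2 | 0.8 | about 12% |

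In the Step 2 simulation (log-odds 0.6, correlation 0.9, about 20% missing) it rejected in 95% of MAR trials, 4.9% of MCAR trials and 4.5% of MNAR trials where dropout depended on the unseen change. There it sent MAR data to the bounds and MNAR data to LOCF.

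**Step 5. The bounds.** The article does not say whether the cases are applied in opposite directions in the two arms. If they are, with share d missing per arm and an assumed best-to-worst HbA1c gap g, the difference runs over (1 − d) × 0.7 ± d × g. At d = 20%, g = 3: 0.56 ± 0.60, or −0.04 to 1.16. At d = 5%, g = 2: 0.665 ± 0.10, or about 0.57 to 0.77. Both are before sampling error.

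**The case against.** A reader might infer that the primary result is biased or uninformative whichever branch is taken. The documents do not support that. They give no dropout rate; at about 5% missing, LOCF costs one point of power and the bounds still inform. Retrieval of laboratory records and the termination visit may keep missingness low. That stands, with limits: retrieval may help HbA1c more than C-peptide, a termination value is not a month-24 value, and neither step corrects the rule for what remains missing.

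A reader might also infer that LOCF gives too small a standard error. It does not do so systematically. Each patient contributes one real observation, and under 20% MCAR dropout the simulated empirical SD (0.219) matched the mean model standard error (0.218–0.223). The fault is bias.

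Three further points have weight. Linear growth is an assumption, and it is weaker for HbA1c, since tablets are stepped up on 3-monthly HbA1c and the Background cites stable values on insulin. The upper type I error figures need threefold differential dropout. The best/worst comparison can be read as a sensitivity analysis; that it replaces the primary estimate is an inference from its role in the final analysis.

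The slope and area-under-the-curve analyses in the Analysis plan are additional and do not replace the rule. It cannot be excused as detail left to an analysis plan, because the article states the test and both actions.

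**Conclusion.** The point holds on the logic with high confidence: the check cannot establish MAR, LOCF is not justified by MAR, and missingness that a MAR analysis could handle is sent to bounds with no stated values.

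The size is less certain, because every magnitude rests on assumed dropout. With equal dropout of 5–20% at mean month 12 and a linearly building effect, HbA1c power falls from 90% to 89–83%. With unequal dropout and no true effect, the spurious C-peptide difference is 0.01–0.04 nmol/l and type I error about 5–9%. The check misclassifies MAR data in about 12–95% of simulated trials at 12% missing, depending on the assumed dropout slope and within-patient correlation, so no single rate should be quoted. The moderate scenarios give modest bias, so this is something that should be fixed rather than a defect that invalidates the plan.

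**What to change.** Delete the test of missing at random and the LOCF rule. Prespecify one primary analysis valid under MAR, without a data-driven choice, using the Analysis plan's covariates (baseline value, GAD, age, sex). Either of these would serve:

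- a mixed model on all 3-monthly values with treatment, visit and treatment-by-visit terms, the 24-month contrast being the primary estimate; or
- multiple imputation of the month-24 value using the interim visits.

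Keep best/worst-case or delta-shift analyses as labelled sensitivity analyses. State the values used and whether they are applied in the same or opposite directions in the two arms. Keep the laboratory-record retrieval and the termination visit, and record the date of each value so that it enters the analysis at its actual time.

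The mixed model's validity under MAR rests on theory and was not simulated here. For comparison, baseline-adjusted complete-case analysis gave 0.68 against a true 0.70 with about 21% MAR dropout, where LOCF gave 0.62.

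The cost is protocol or analysis-plan wording. SPSS, the named software, fits both methods, and no new data are needed. The change should be made before outcome data are seen.
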